### Study design

This pragmatic, single-centre, non-randomised, quasi-experimental cohort study will evaluate clinical and radiological outcomes in two distinct patient cohorts. The comparator cohort is defined as *usual care*; general radiologist reporting of CTPA. This cohort will consist of patients recruited retrospectively, prior to implementation of the AI. The intervention cohort is defined as *integrated AI technology AND usual care*; general radiologist reporting of CTPA with access to AI technology for acute PE detection. This cohort will consist of patients recruited prospectively, following the implementation of the AI.

The study will consist of three distinct phases. The pre-implementation and post-implementation phases will derive the comparator and intervention cohorts, respectively. The implementation phase will ensure installation, testing and appropriate training of the AI technology. Figure 1 outlines the study structure.

**Figure 1 F1:**
[figure not shown]
Study schedule and recruitment. AI, artificial intelligence.

### Study aim

To evaluate the diagnostic performance of integrated AI for the detection of PE and RHS on CTPA and establish the clinical and economic impact of AI assistance on the diagnosis, risk stratification and downstream management of patients presenting with suspected acute PE.

### Study objectives

The retrospective cohort analysis will assess the diagnostic performance of AI in detecting acute PE and quantifying associated RHS. The study will compare AI outputs against routine clinical radiology reports as well as a redefined ground truth through expert thoracic radiologist review of a subset of retrospective CTPAs. The prospective cohort analysis will assess the real-world impact of AI integration on clinical practice, including risk stratification, treatment decisions and patient outcomes. The study will compare concordance of acute PE risk stratification and patient management with local protocols and European Society of Cardiology guidelines.^11^ The study will also assess the clinical-cost impact of AI integration into radiology workflows.

Finally, the study will explore the perspective of key stakeholders, including radiologists and referring clinicians, on the implementation and use of AI technology before, during and after deployment.

### Study population and setting

Study participants will be recruited from consecutive, clinically indicated CTPAs performed for the assessment of acute PE at Royal United Hospitals Bath NHS Foundation Trust in England. Scans from both inpatient and outpatient settings will be included. Ethical approval for participant inclusion has been granted by West of Scotland Research Ethics Service (23/WS/0067, 3 May 2023).

The pre-implementation (comparator) cohort will be retrospectively identified over a 12-month period preceding AI deployment. Following a 1 month implementation phase, the post-implementation (intervention) cohort will be prospectively recruited over the subsequent 12 months. Prospective recruitment will complete on 7th January 2025.

All participants will meet the following eligibility criteria:

#### Inclusion criteria

Adults over 18 years old.CTPA performed for the clinical assessment of acute PE.

#### Exclusion criteria

Participants will not be eligible for inclusion in the study if any of the following are true:

Aged under 18 years old.Registered with the national opt-out scheme for research.CTPA performed for reasons other than the assessment of acute PE.CTPA reported by external radiologist.CTPA scan which is incomplete or discontinued.

Patients whose CTPA was reported by an external radiologist will be excluded due to difficulty confirming the reporting radiologist’s access to existing AI software. Patients will also be excluded if the clinical indication for CTPA is unrelated to acute PE. The AI software is solely licenced for the assessment of acute PE. No substantial amendments have been made to the eligibility criteria since study inception.

### Sample size

As a pragmatic real-world quasi-experimental assessment of AI integration, formal power calculations were not feasible. Based on historic imaging volumes, it is anticipated that approximately 3500 eligible CTPAs will be identified across the 24-month recruitment period and that the prevalence of acute PE will be between 12% and 15%.

### Screening and consent

The research team will establish the comparator and intervention cohorts by screening all consecutively reported CTPAs identified through the radiology information system (RIS). Consent was explicitly discussed with patient and public involvement (PPI) participants during the design and planning of the study. PPI participants were supportive of automated AI assessment at the time of CTPA imaging and did not express concerns over its use as a decision-support tool. The ethics committee waived the need for formal patient consent given that all AI outputs will be reviewed and verified by a human radiologist prior to inclusion in any clinical reports. This approach was deemed acceptable due to the absence of direct patient risk.

### Participant data

Clinical, radiological and patient-related outcomes will be extracted for each participant using a combination of electronic and paper-based systems. Primary data sources will include electronic health records, integrated care records, RIS and physical patient notes where relevant. Data extraction will be conducted by trained members of the research team using a pre-specified case report form (CRF) to ensure consistency.

The following data types will be collected for each participant:

Demographics: age and sex.Anthropometrics: height, weight and body mass index.Referral context: date and time, outpatient or inpatient location.Admission/discharge details: admission and discharge date and time.Comorbidities: structured past medical history entries and coded diagnoses.Physiological parameters: vital signs closest to the time of CTPA request (ie, heart rate, blood pressure, oxygen saturation, respiratory rate).Biochemistry markers: including, but not limited to, d-dimer, troponin, brain natriuretic peptide.Imaging history: chest radiography, echocardiography, lower extremity limb Doppler ultrasound.Medication history: including, but not limited to, anticoagulants, antiplatelets and time to anticoagulation initiation.Patient management details: time of first clinical review, location of ongoing care and referrals to respiratory, thrombosis and haematology clinics.Acute PE severity assessment: simplified pulmonary embolism severity index (sPESI) and the Geneva Score calculated based on recorded clinical parameters.^20 21^Clinical outcomes up to 12 months after their CT data: including, but not limited to, intensive care admission, haemodynamic instability, thrombolysis administration, re-presentation to the emergency department, re-admission to the hospital, major and minor bleeding events and all-cause mortality.

### Interventions

#### CT report interpretation

All radiology reports for consecutive CTPAs in the comparator and intervention cohorts will be reviewed by a respiratory registrar with 8 years’ clinical experience. The reports will be classified as either positive or negative for acute PE. In cases of uncertainty, adjudication will be performed by a second senior clinician.

The same registrar and a second clinician, blinded to each other’s decisions, will independently assess the reports for radiologist assessment of RHS. Reports will be categorised as either positive, negative or ‘no comment’ for RHS. Discrepancies will be resolved through discussion and, if required, arbitration from a third clinician. This approach will establish a consistent comparator for evaluating AI outputs.

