## Introduction

### Background

 Pulmonary embolism (PE) is a potentially fatal condition that may cause right ventricular failure and death if not recognised and treated promptly. In the UK, PE accounts for almost 70 000 hospital presentations and 37 000 hospital admissions per year.^1^ This places a substantial financial and operational burden on the NHS. Although it is difficult to know precise cost estimates, the total cost burden for venous thromboembolism is estimated at £640 million per year.^2^ Furthermore, the incidence of PE is rising.^3^,^5^ This trend can be partially explained by the increasing availability and improved quality of diagnostic imaging. However, demographic and clinical factors, such as increased survival among patients with major prothrombotic comorbidities and obesity, are also likely to contribute to this increase.^6^

Although falling, mortality from PE remains significant. It accounts for up to 6.5 deaths per 100 000 population per year.^6^ The reduction in mortality is attributed to improved interventions, including direct oral anticoagulants, better management guidelines^7^ and increased diagnosis of smaller, subsegmental emboli.^8^ However, despite advances in PE detection and clear national guidance on acute PE treatment, risk stratification and management are still performed poorly.^9^

Radiological imaging plays a critical role in the PE pathway. Multi-detector CT pulmonary angiography (CTPA) is considered the gold standard imaging modality for PE diagnosis. CTPA can also provide important, prognostically relevant information on right heart strain (RHS).^10 11^ This includes reversal of the right ventricular to left ventricular ratio (RV:LV), interventricular septal straightening and contrast reflux in the inferior vena cava. These indirect markers can inform risk stratification and subsequent clinical medical management.

The NHS Long Term Plan outlines the importance of innovative, affordable technologies to improve diagnosis, risk assessment and treatment of respiratory conditions, including PE.^12^ Achieving this depends on accurate image interpretation and timely communication of findings. However, national audits, including the National Confidential Enquiry into Patient Outcome and Death, have highlighted deficiencies in PE reporting and downstream clinical.^9^

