#### AI technology and application

The AI solutions under evaluation are provided by AIDOC, who offer two FDA approved AI solutions for acute PE detection and assessment of the RV:LV ratio. The latter AI tool is created by IMBIO for quantification of RHS. The AI solutions are both CE-marked and operate within UK information governance standards.

The AI solution uses Digital Imaging and Communications in Medicine (DICOM) data that is sent to the on-premises AIDOC Orchestrator from one or more DICOM sources (picture archiving and communication system (PACS), vendor neutral archive, DICOM router or modality scanners). The Orchestrator uses AI-based computer vision to identify the anatomy in the image series and determines which AI algorithms can be run. It then de-identifies the DICOM before sending it to the AIDOC cloud environment for analysis. No patient identifiable data leaves the customer network (ie, the Trust), and no communication is initiated from the cloud. The Orchestrator polls the cloud for AI results, which are typically available within 2–6 min. Once available, the Orchestrator downloads the AI results via a secure tunnel connection and distributes them accordingly (typically via prioritisation alerts in the AIDOC Desktop App and via radiology worklist prioritisation). Figure 2 illustrates the data flow between the Trust, cloud environment and Orchestrator.

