### Statistical analysis

#### Clinical and radiological outcomes

Our primary outcome will be the proportion of patient decisions made in line with evidence-based best practice guidelines after introducing AI technology within CTPA reporting. Secondary outcomes relate to acute PE detection, RV:LV ratio quantification and clinical and operational endpoints including mortality, length of stay, readmission, follow-up and cost to NHS (table 1).

**Table 1 T1:** Primary, secondary and additional outcomes

Outcome measure	Measure description
Primary outcome measure	
Proportion of patient decisions made in line with evidence-based best practice guidelines after introducing AI technology within CTPA reporting	Comparison before and after AI introduction
Secondary outcome measures	
Rate of acute PE detection with AI technology	True positives and true negatives
Rate of discordant acute PE cases	False positive and false negative rate with acute PE detection
AI failure rate for acute PE detection	Proportion of scans unable to be interpreted by AI despite suitable CTPA acquisition
Rate of RV:LV detection with AI technology	True positive and true negative
Rate of discordant RV:LV detection	False positive and false negative
Failure rate for automated RV:LV ratio	Proportion of scans unable to calculate automated RV:LV ratio despite suitable CTPA acquisition
30-day mortality	Patient mortality (death) at 30-days post-PE diagnosis. Comparison before and after AI introduction
12-month mortality	Patient mortality (death) at 12 months post-PE diagnosis. Comparison before and after AI introduction
Hospital admission and bed days for acute PE	Comparison before and after AI introduction
Time to anticoagulation in PE cases	Comparison before and after AI introduction
Time from CTPA to discharge	Comparison before and after AI introduction
PE risk stratification rates (low, intermediate low, intermediate high and high risk)	Comparison before and after AI introduction
Cost to NHS for acute PE	Comparison before and after AI introduction
End-user (clinician and radiologist) acceptability of AI technology	Quantified metrics from a non-validated questionnaire to evaluate end-use experience of integrated AI radiology reporting
Referral rates to outpatient follow-up (respiratory, thrombosis, haematology)	Comparison before and after AI introduction
Diagnostic rate of chronic thromboembolic pulmonary hypertension	Comparison before and after AI introduction
Additional outcome measures	

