#### Artificial intelligence accuracy

We will evaluate AI performance against both the original radiology reports and expert thoracic radiologist reviews, which will serve as the clinical reference standard. Agreement between modalities will be assessed using Cohen’s kappa and measures of diagnostic test performance.

The research team will also review all PE-positive and discrepant cases to evaluate the potential for the AI software to act as a clinical safety net for the detection of acute PE.

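### Against routine reports, an AI that measures only the RV:LV ratio is scored on right heart strain overall, so a correct normal ratio can count as a false negative

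*Protocol article*

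**What the plan says.** - **What RHS means.** The Background section describes RHS on CT by three signs: "This includes reversal of the right ventricular to left ventricular ratio (RV:LV), interventricular septal straightening and contrast reflux in the inferior vena cava".
- **What the AI returns.** The section on AI technology and application describes "two FDA approved AI solutions for acute PE detection and assessment of the RV:LV ratio", and adds: "The latter AI tool is created by IMBIO for quantification of RHS". The section on the intervention cohort mentions RV:LV overlays. No septal or IVC output is described.
- **How reports are coded.** Under CT report interpretation, two clinicians read each report independently: "Reports will be categorised as either positive, negative or ‘no comment’ for RHS". The code has no level for the marker the radiologist relied on. Its purpose is stated: "This approach will establish a consistent comparator for evaluating AI outputs".
- **How the result is labelled.** Table 1 lists RV:LV detection by true positives and true negatives, and "Rate of discordant RV:LV detection" by false positives and false negatives.
- **Which comparators are used.** The section on AI accuracy says: "We will evaluate AI performance against both the original radiology reports and expert thoracic radiologist reviews". The Study objectives section likewise names both. The Reference standard section limits the blinded expert review to a 4-month run of consecutive scans in the comparator cohort.

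**The concern.** The AI output is a single ratio. The report code covers any sign of strain and has three levels. The outcome labels are binary and specific to the ratio. When the first is scored against the second and reported under the third, part of the apparent error reflects a difference in what is being judged.

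Two situations matter. In the first, the report calls strain on septal straightening or IVC reflux while the ratio is normal. The AI is right about the ratio and is still scored as a miss. In the second, the report says nothing about strain. Such a report fits no cell of a true/false table. It may be common, since the section on challenges in current practice says that reporting of the ratio is frequently inconsistent or absent, though it gives no rate.

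At stake is how one pair of secondary outcomes is read. A sound ratio tool could be reported as missing cases because radiologists used other signs.

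**Working it through.** The article gives no accuracy target or power figure for this outcome, so there is nothing to reproduce. The check has three steps.

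**1. How much of the study relies on the report code.** Inputs from the Sample size section: about 3500 scans over 24 months, PE prevalence 12 to 15%. Even accrual is assumed.
- Expert subset: 3500 × 4/24 ≈ 583 scans, with 583.3 × 0.12 = 70 to 583.3 × 0.15 ≈ 88 PEs.
- Remainder: 1 − 4/24 ≈ 83% of scans, including the whole intervention cohort. Routine reports are the only planned comparator there.
- PEs per cohort: 1750 × 0.12 = 210 to 1750 × 0.15 ≈ 262.

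**2. An error-free ratio scored against an error-free report of any strain.** The following are assumptions, not figures from the article:
- a = share of PE cases with a raised ratio (0.3 or 0.5)
- s = share of normal-ratio cases with another sign (0.05 or 0.15)
- o = share of reports with 'no comment', unrelated to the findings

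True positives = n·a·(1 − o). 'False negatives' = n·(1 − a)·s·(1 − o). The factor (1 − o) cancels, so apparent sensitivity = a / [a + (1 − a)·s].

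| a | s | Apparent sensitivity | 'False negatives' among 210 PEs, o = 0 |
|---|---|---|---|
| 0.3 | 0.05 | 0.300/0.335 = 0.90 | 7.4 |
| 0.3 | 0.15 | 0.300/0.405 = 0.74 | 22.1 |
| 0.5 | 0.05 | 0.500/0.525 = 0.95 | 5.3 |
| 0.5 | 0.15 | 0.500/0.575 = 0.87 | 15.8 |

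In this model the loss of sensitivity is the same whether 'no comment' is excluded or counted as negative.

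**3. The 'no comment' reports.** The result depends on a rule the article does not give.
- Excluded: no false positives, specificity 1.00. Only scans on which the radiologist commented remain.
- Counted as negative: 'false positives' = n·a·o. With n = 210 and a = 0.3, this is 210 × 0.3 × 0.2 = 12.6 at o = 0.2, and 210 × 0.3 × 0.5 = 31.5 at o = 0.5.

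**Check of the remedy.** With a ratio-specific code (s = 0) and 'no comment' kept out of the two-by-two table, the same error-free tool has sensitivity, specificity and kappa of 1.00. The apparent errors come from the scoring.

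**The case against.** The best defence is that the report code is not the reference standard. The article sets up blinded review by cardiothoracic radiologists for that purpose and separates it from the comparison with routine reports. Table 1 does not say which comparator supplies the RV:LV counts. This stands, and it limits the point to the report-based comparison. It does not remove it: the code is expressly declared a comparator for AI outputs, and the expert review covers about one sixth of the scans.

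A second defence is that the plan already contains safeguards. Every discrepancy between AI and report in the intervention cohort is to be reviewed, and Cohen's kappa is planned as a measure of agreement. Case review could show that a report rested on septal or IVC signs, but the article does not say that it would correct the Table 1 rates. Kappa avoids the word 'false' but carries the same mismatch: with 'no comment' excluded and a = 0.3, the error-free tool has kappa 0.92 (s = 0.05) or 0.77 (s = 0.15).

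Third, the tool is described as quantifying RHS, so asking how its output compares with what radiologists say about RHS is a fair pragmatic question. It is, as a question of agreement. It does not justify RV:LV error labels.

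Finally, the expert form is not shown and may already hold the ratio as a separate item. The article cannot settle this, so its absence is not claimed here.

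**Conclusion.** The mismatch is in the text and affects secondary outcomes only. Against routine reports, an error-free RV:LV ratio is scored as a false negative whenever strain was called on another sign alone. Under the assumed values, apparent sensitivity lies between 0.74 and 0.95. The true size depends on how often reports call strain with a normal ratio, which the article does not give. The 83% share assumes even accrual. The primary outcome and the expected recruitment are unaffected.

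A reader might infer two stronger claims that the documents do not support. One is that 'no comment' reports will produce false positives. The article keeps them as a separate category and nowhere counts them as negative, so this holds only under an unstated rule. The other is that the RV:LV outcome is uninformative about the tool. The expert-based comparison can be valid, provided the experts record the ratio itself.

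**What to change.** 1. Take RV:LV true and false positive and negative rates from the 4-month expert subset only, scored on the RV:LV ratio as recorded by the experts, separately from septal straightening and IVC reflux.
2. For routine reports, add one field to the existing double reading: which marker the report cites.
3. Against reports, present a table of positive, negative and 'no comment' rows by AI result. Call it agreement, and do not label the off-diagonal cells false positives or false negatives.
4. Report the number of AI-raised ratios in the 'no comment' row. This shows the information the tool adds where the radiologist was silent.
5. Amend the RV:LV rows of Table 1 to match.

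The cost is one coding field, confirmation (or addition) of the ratio as an item on the expert form, and lower precision. With 70 to 88 PEs in the subset and an assumed 30 to 50% with a raised ratio, sensitivity would rest on about 70 × 0.3 = 21 to 88 × 0.5 = 44 cases. At an assumed sensitivity of 0.90, the approximate 95% half-width is 1.96 × √(0.9 × 0.1/21) ≈ 0.13 to 1.96 × √(0.9 × 0.1/44) ≈ 0.09.

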#### AI technology and application

The AI solutions under evaluation are provided by AIDOC, who offer two FDA approved AI solutions for acute PE detection and assessment of the RV:LV ratio. The latter AI tool is created by IMBIO for quantification of RHS. The AI solutions are both CE-marked and operate within UK information governance standards.

The AI solution uses Digital Imaging and Communications in Medicine (DICOM) data that is sent to the on-premises AIDOC Orchestrator from one or more DICOM sources (picture archiving and communication system (PACS), vendor neutral archive, DICOM router or modality scanners). The Orchestrator uses AI-based computer vision to identify the anatomy in the image series and determines which AI algorithms can be run. It then de-identifies the DICOM before sending it to the AIDOC cloud environment for analysis. No patient identifiable data leaves the customer network (ie, the Trust), and no communication is initiated from the cloud. The Orchestrator polls the cloud for AI results, which are typically available within 2–6 min. Once available, the Orchestrator downloads the AI results via a secure tunnel connection and distributes them accordingly (typically via prioritisation alerts in the AIDOC Desktop App and via radiology worklist prioritisation). Figure 2 illustrates the data flow between the Trust, cloud environment and Orchestrator.

